#### Primary outcome

2.6.1

**Chronic pain acceptance**. Chronic Pain Acceptance will be assessed using the Chronic Pain Acceptance Questionnaire (CPAQ) (McCracken et al., 1999) measuring the extent to which individuals are willing to experience pain while engaging in meaningful activities. The 20-item are rated on a 7-point scale ranging from 0 (“Never true”) to 6 (“Always true”). The questionnaire comprises two subscales: Activity Engagement (AE), reflecting participation in daily activities despite pain, and Pain Willingness (PW), assessing the degree to which individuals refrain from attempts to control or avoid pain. Subscale scores are summed to derive a total score ranging from 0 to 120, with higher scores indicating greater levels of pain acceptance. The Italian validation of the CPAQ reported good internal consistency for the Activity Engagement subscale and total score (Cronbach's α > 0.80), and acceptable reliability for the Pain Willingness domain (α > 0.70) (Bernini et al., 2010).

#### Secondary outcomes

2.6.2

**Pain intensity and pain interference**. The Brief Pain Inventory (BPI) (Cleeland, 1989) consists of 11-item divided into two subscales. The first subscale assesses pain severity (Severity score, BPI-SS) through four Numerical Rating Scales ranging from 0 (“no pain”) to 10 (“worst imaginable pain”), evaluating current pain, worst pain, least pain and average pain over the past 24 h. The second subscale measures pain interference (Interference score, BPI-IS) with daily activities, walking ability, mood, sleep, work, relationships with others and enjoyment of life, using Numerical Rating Scales ranging from 0 (“does not interfere”) to 10 (“completely interferes”). The BPI-SS is calculated as the mean of four severity items, and the BPI-IS as the mean of seven interference items. Therefore, the maximum possible score for both dimensions is 10. The Italian version of the Brief Pain Inventory has demonstrated good internal consistency, with Cronbach's alpha coefficients ranging from 0.77 to 0.91 across severity and interference subscales, as well as good test–retest reliability, supporting its use in Italian chronic pain populations (Caraceni et al., 1996).

**Quality of life**. The EuroQol-5D-3L (EQ-5D-3L) (Group, 1990) is a standardized instrument developed to measure QoL. The questionnaire consists of two parts. The first part includes five dimensions: mobility, self-care, usual activities, pain/discomfort and anxiety/depression. Each dimension is divided into three severity levels ranging from 1 (“no problems”) to 3 (“extreme problems”). Health states are converted into utility index scores using country-specific value sets, with higher scores indicating better perceived health. The second part includes a VAS indicating current perceived health status on a scale from 0 (“worst imaginable health”) to 100 (“best imaginable health”). The Italian version demonstrated good reliability, with Cronbach's alpha = 0.73 (Savoia et al., 2006).

**Sleep quality**. The Mini Sleep Questionnaire (MSQ) (Zomer, 1985) assesses sleep quality, considering both sleep and wakefulness factors. The questionnaire consists of 10-item, which are rated on a Numerical Rating Scale from 1 (“Never”) to 7 (“Always”) to indicate how well it describes the participant's experience during the previous week. Higher scores indicating poorer sleep quality. Subscale scores were computed for sleep and wakefulness domains, with established clinical cut-offs of >16 and >14, respectively. The Italian version of the MSQ showed good internal consistency (Cronbach's alpha = 0.77), good test–retest reliability (ICC = 0.82) and a factor analysis confirming two dimensions (sleep and wakefulness), both with Cronbach's alpha = 0.75. Optimal cut-off values (>16 for sleep and >14 for wakefulness) have been identified, with an area under the curve greater than 0.80 (Natale et al., 2014).

**Central sensitization**. The Central Sensitization Inventory (CSI) (Mayer et al., 2012) measures current health symptoms related to central sensitization. The instrument includes 25-item rated on a 0 (“never”) to 4 (“always”) scale, yielding a total score ranging from 0 to 100, with higher scores indicating greater symptom severity. A cut-off score of ≥40 has demonstrated good sensitivity and specificity in identifying individuals with central sensitization syndromes. The CSI also includes a supplementary checklist (Part B) assessing prior diagnoses of central sensitization–related conditions (e.g., fibromyalgia, irritable bowel syndrome, migraine). These items are not included in the total score but provide descriptive clinical information. The Italian version demonstrated good internal consistency (Cronbach's alpha = 0.87), ranging from 0.86 to 0.87 if an item is removed (Chiarotto et al., 2018).

**Pain catastrophizing**. The Pain Catastrophizing Scale (PCS) (Sullivan et al., 1995) is used to assess the level of catastrophic thinking associated with pain. The scale consists of 13-item rated on a 5-point Likert scale, where 0 indicates “not at all” and 4 indicates “always”. The PCS includes three subscales reflecting rumination, magnification, and helplessness. The total score ranges from 0 to 52, with higher scores indicating greater levels of pain catastrophizing. A commonly adopted clinical cut-off is ≥30, indicating clinically relevant levels of catastrophizing. The Italian version of the PCS has demonstrated excellent internal consistency (Cronbach's alpha = 0.92) (Monticone et al., 2012).

**Psychological flexibility**. The Multidimensional Psychological Flexibility Inventory (MPFI-24) (Grégoire et al., 2020; Landi et al., 2026) is a self-report instrument consisting of 24-item measuring the six core processes of PF (12-item) and the six processes of psychological inflexibility (12-item). Items are rated on a 6-point Likert scale ranging from 1 (“Never true”) to 6 (“Always true”), referring to experiences over the previous 2 weeks. Flexibility processes include acceptance, cognitive defusion, present-moment awareness, self-as-context, values, and committed action, whereas inflexibility processes include experiential avoidance, cognitive fusion, lack of present-moment awareness, self-as-content, lack of values clarity, and inaction. Global scores for psychological flexibility and inflexibility can be derived. The Italian version of the MPFI has shown excellent internal consistency (Cronbach's alpha = 0.94 for both global psychological flexibility and inflexibility), with subprocesses ranging from 0.85 to 0.94 (Landi et al., 2021, 2026).

**Self-efficacy**. The Pain Self-Efficacy Questionnaire (PSEQ) (Nicholas, 2007) will be used to assess individuals' confidence in performing activities despite pain. It consists of 10-item are rated on a 7-point Likert scale from 0 (“Not at all confident”) to 6 (“Completely confident”), producing total scores ranging from 0 to 60, with higher scores reflecting greater perceived self-efficacy. The Italian version of the PSEQ demonstrated excellent internal consistency (Cronbach's alpha = 0.94) and good test–retest reliability (ICC = 0.82) (Chiarotto et al., 2015).

**Coping**. The Chronic Pain Coping Inventory (CPCI) (Romano et al., 2003) evaluates the frequency of cognitive and behavioral coping strategies used during the previous week via 42-item. The questionnaire comprises eight subscales reflecting distinct coping domains, including guarding, resting, asking for assistance, relaxation, task persistence, exercise and stretching, coping self-statements, and seeking social support. Each subscale yields scores ranging from 0 to 7, with higher scores indicating more frequent use of the respective coping strategy. The Italian version has shown good internal consistency (Cronbach's alpha = 0.71–0.80) and reliability (ICC = 0.70–0.85 and >0.85 across all subscales) (Monticone et al., 2013).

**Anxiety**. The Generalized Anxiety Disorder scale (GAD-7) (Spitzer et al., 2006; Löwe et al., 2008) assesses symptoms of anxiety and counts on 7-item. Each item describes a specific symptom experienced over the past 14 days and is rated on a four-point scale: 0 (“Not at all”), 1 (“Several days”), 2 (“More than half the days”) and 3 (“Nearly every day”). Total scores range from 0 to 21 and reflect anxiety severity. Established severity cut-offs are 5 (mild), 10 (moderate), and 15 (severe anxiety), with scores ≥10 indicating clinically significant anxiety. The Italian GAD-7 has demonstrated good internal consistency (Cronbach's alpha = 0.918) (Ivziku et al., 2019).

**Depression**. The Patient Health Questionnaire (PHQ-9) (Kroenke and Spitzer, 2002) is a self-report instrument made up of 9-item used to assess depressive symptom severity. It screens eight psychological disorders, distinguishing between threshold DSM-IV diagnoses (major depressive disorder, panic disorder, other anxiety disorder, bulimia nervosa) and subthreshold conditions characterized by fewer symptoms than required for formal diagnosis (other depressive disorder, probable alcohol abuse/dependence, somatoform disorder, and binge eating disorder). Participants indicate how often each symptom has occurred over the past 2 weeks on a scale from 0 (“Not at all”) to 3 (“Nearly every day”), resulting in a total score from 0 to 27. Severity thresholds are 5 (mild), 10 (moderate), 15 (moderately severe), and 20 (severe depression), with scores ≥10 typically indicating clinically relevant depressive symptomatology. Item 9 assesses passive thoughts of death or self-harm and will be monitored according to trial safety procedures. The Italian version of the PHQ-9 has demonstrated good internal consistency (with Cronbach's alpha coefficients ranging from 0.86 to 0.92) (Mazzotti et al., 2003).

At each of the seven intervention weeks, participants will complete a VAS assessing their perceived sleep quality for that week (“How would you rate the quality of your sleep during this week?”), ranging from 0 (“worst imaginable sleep quality”) to 100 (“best imaginable sleep quality”).

Participants will also answer a weekly question regarding potential changes in their pharmacological treatment for chronic pain management.

**Week 1:** “Compared with what you reported at the pre-intervention assessment, have there been any changes in your pharmacological treatment for chronic pain management?”**Subsequent weeks:** “Compared with the previous week, have there been any changes in your pharmacological treatment for chronic pain management?”

Response options will be: “No, there have been no changes” or “Yes, there have been changes.” If changes are reported, participants will be prompted to specify the type of modification: “increased dosage of the same medication(s),” “reduced dosage of the same medication(s)” or “administration of different medication(s).”

### Cost-effectiveness analysis

2.7

To conduct the cost-effectiveness analysis, data will be collected from the beginning of the programme to the final follow-up, and the resources required to deliver the intervention itself will also be calculated. Service use by patients will be recorded through the MobACT platform, covering the use of additional treatments in hospitals and centers, other prescribed therapies, hospital admissions, emergency department visits, outpatient appointments, service utilization, medications and assistive devices.

To enable economic analysis, the questionnaires conducted through the *Iterapi* platform will also collect information on days of work missed, recreational activities, private expenses (e.g., privately paid therapies, travel costs for treatment), informal care, welfare benefits and lost work hours (including those of family members and friends) required to manage the pain condition. The cost-effectiveness analysis will be conducted from both a healthcare perspective and a societal perspective, following existing guidelines. The Second Panel on Cost-Effectiveness in Health and Medicine recommends that all studies report a reference case analysis based on the healthcare sector perspective and another reference case analysis based on the societal perspective.

The Impact Inventory (Sanders et al., 2016), which lists the health and non-health effects of an intervention, makes the economic evaluation more explicit and transparent. For the healthcare sector perspective, the total programme cost per participant will be calculated using the resource-costing method, which includes personnel, supplies and equipment costs (e.g., web hosting service, software maintenance) needed to deliver MobACT. For the societal perspective, the cost of patient time, transportation costs and the cost of unpaid productivity loss due to illness will be calculated.

Specifically, to estimate resource use and costs, targeted questions were formulated by adapting and implementing the questionnaire designed for adolescents with Chronic Pain—parent report (Client Service Receipt Inventory for Adolescents with Chronic Pain–Parent Report) (Sleed et al., 2005), which was used as a reference. This inventory is an adaptation of the CSRI (Beecham and Knapp, 2001) specifically for parents of adolescents with Primary Chronic Pain. The Client Service Receipt Inventory (CSRI) (Beecham and Knapp, 2001) is a tool for estimating direct and indirect costs and is essential in health and health service economics research. It systematically collects data on service use and associated costs, providing a detailed account of the various services utilized by individuals.

The effectiveness of the intervention will be measured based on changes in Quality-Adjusted Life Years (QALYs) and patient productivity (work hours and income). Data collected from the EQ-5D-3L can be converted into a single summary index value, which is essential for calculating QALYs. QALYs are a measure that combines both the quality and quantity of life lived. This metric is used to assess the value of medical interventions by considering the number of life years added by the intervention, adjusted for the quality of those years (Gallego et al., 2024). Each health state described by the EQ-5D-3L has an associated utility value, typically ranging from 0 (equivalent to death) to 1 (perfect health). By multiplying the time spent in a given health state by its utility value, QALYs provide a standardized method for comparing the effectiveness of different treatments and informing healthcare decision-making. One year in a state of “perfect health” equals 1 QALY, whereas being deceased equals 0 QALYs. The formula for calculating QALYs is as follows: number of years of treatment multiplied by the quality-of-life coefficient. For each dimension of the EQ-5D-3L, a score is assigned and then multiplied together to obtain the quality-of-life coefficient, which will be multiplied by the number of years. These data will be collected at pre-intervention (T0), post-intervention (T1) and 6-month follow-up (T2; intervention group only). The use of the EQ-5D-3L to derive QALYs ensures a robust and consistent approach to evaluating and comparing health outcomes across patient populations and different treatments.

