All analyses will be performed under the intention-to-treat principle whenever feasible, ensuring that participants are analyzed within their originally assigned groups regardless of treatment adherence. Sensitivity analyses will be conducted to evaluate the robustness of the findings under different assumptions regarding missing data handling (e.g., complete-case vs. imputed datasets), model specifications, and adjustment for relevant baseline covariates.

Qualitative data from the clinical interviews will be analyzed using reflexive thematic analysis in accordance with Braun and Clarke's framework (Braun and Clarke, 2006). A primarily inductive analytic approach will be adopted to allow themes to emerge from participants' narratives while remaining sensitive to ACT-related and digital-intervention processes. Data collection will continue until thematic saturation is reached, defined as the point at which no substantially new themes relevant to the research questions are identified in consecutive interviews. Rigor and trustworthiness will be supported through independent coding of a subset of transcripts by at least two researchers, regular analytic discussions, reflexive memoing, documentation of coding decisions in an audit trail and reporting guided by relevant qualitative reporting standards such as COREQ (Tong et al., 2007).

The economic evaluation will be integrated with the clinical data and will rely on the calculation of Quality-Adjusted Life Years (QALYs) derived from EQ-5D-3L utility scores. Incremental cost-effectiveness ratios will be estimated by comparing the costs and outcomes associated with MobACT relative to the waitlist condition, adopting both healthcare-sector and societal perspectives. The uncertainty surrounding these estimates will be examined through non-parametric bootstrapping procedures and appropriate graphical representations, such as cost-effectiveness planes and acceptability curves. The trial protocol and statistical analysis plan will be made publicly accessible through the ClinicalTrial.gov registry (NCT07270588).

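### The stated QALY formula multiplies EQ-5D-3L dimension scores together, which contradicts the value-set utilities named elsewhere in the protocol and does not give a utility

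*Protocol article*

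**What the plan says.** Section 2.7 (Cost-effectiveness analysis) gives an explicit QALY formula: "number of years of treatment multiplied by the quality-of-life coefficient". The next sentence explains the coefficient: "For each dimension of the EQ-5D-3L, a score is assigned and then multiplied together to obtain the quality-of-life coefficient", after which it is multiplied by the number of years.

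The article describes the calculation differently in three other places:

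- Section 2.6.2 (Secondary outcomes, quality of life): "Health states are converted into utility index scores using country-specific value sets, with higher scores indicating better perceived health".
- Section 2.7, a few sentences before the formula: "Each health state described by the EQ-5D-3L has an associated utility value, typically ranging from 0" for death up to 1 for perfect health. QALYs are there obtained "By multiplying the time spent in a given health state by its utility value", and one year in perfect health counts as 1 QALY.
- Section 2.8 (Data analysis): the economic evaluation relies on "Quality-Adjusted Life Years (QALYs) derived from EQ-5D-3L utility scores".

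The only dimension-level values in the article are in section 2.6.2: "Each dimension is divided into three severity levels ranging from 1" (no problems) to 3 (extreme problems).

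Section 1.1 restricts the cost-effectiveness comparison with waitlist to T1. Section 2.1 says waitlist participants complete T0 and T1 without access to MobACT, and section 2.4 gives them access after 7 weeks.

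**The concern.** A value set assigns one utility to each five-dimension health state. Multiplying five separately scored dimensions is a different instruction, and an analyst cannot follow both. The article cannot be read as leaving the calculation to the statistical analysis plan, because it prints a formula.

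Section 2.8 builds the incremental cost-effectiveness ratio, the bootstrap, the cost-effectiveness planes and the acceptability curves on these QALYs. If the coefficient is off the utility scale or runs in the wrong direction, the denominator of the ratio is invalid and can change sign. The time term raises a second question, because waitlist participants have no treatment time before T1.

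**Working it through.** **Inputs.** Five dimensions with levels 1, 2, 3 (section 2.6.2); the product rule, the time term and the 0-to-1 utility anchor (section 2.7); a 7-week wait (section 2.4), which is 7/52.18 = 0.134 years. The article gives no utility values, so those used below are assumptions with a range.

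**Step 1: can the stated 0-to-1 scale be reproduced by the product rule?** There are 3^5 = 243 health states. Taking the levels as the scores:

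- 11111 gives 1^5 = 1 (best state)
- 22222 gives 2^5 = 32
- 33333 gives 3^5 = 243 (worst state)

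Only one state, 11111, falls within 0 to 1. The 243 states collapse to 21 distinct products, so very different states share a value: 11121 and 21111 both give 2. The stated scale is not reproduced.

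**Step 2: direction.** Moving from 21232 to 21222 is an improvement in one dimension. The coefficient falls from 2×1×2×3×2 = 24 to 2×1×2×2×2 = 16. Suppose a MobACT participant makes this change linearly over the interval and a waitlist participant stays at 21232, with elapsed time used in both arms:

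- MobACT: 0.134 × (24 + 16)/2 = 2.68
- Waitlist: 0.134 × 24 = 3.22

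The participant who improves scores lower. Both figures also exceed the most that 0.134 years can yield on the article's own anchor, 0.134 × 1 = 0.134 QALY.

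**Step 3: does another simple coding rescue it?** With levels coded 0, 1, 2, the product is nonzero only if every dimension has a problem, which is 2^5 = 32 states. The other 243 − 32 = 211 states, including perfect health, get 0. The article prints no set of dimension scores whose product would equal the value-set index.

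**Step 4: the time term, under both readings.** Put the product aside and use a proper utility u, equal in both arms, so that the true QALY difference is 0.

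- Literal treatment time: MobACT 0.134 × u, waitlist 0 × u = 0. For assumed u from 0.3 to 0.8 the apparent gain is 0.040 to 0.107 QALY (0.080 at u = 0.6).
- Elapsed time: 0.134 × u in both arms, difference 0.

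For comparison, an assumed true utility gain d of 0.02 to 0.10 by T1, accruing linearly, gives 0.134 × d/2 = 0.0013 to 0.0067 QALY. Under the literal reading the artefact would be about 6 times (0.040/0.0067) to 80 times (0.107/0.0013) as large.

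**The case against.** The strongest reply is that the article describes the conventional method in three places (sections 2.6.2 and 2.8, and earlier in 2.7) and gives the product rule once, so the formula is probably a garbled explanation that no analyst would carry out. It is fair that this is an internal contradiction and not an undisputed plan to use the product. It does not remove the point: the product rule is the only text presented as the formula, and nothing in the article says which statement governs.

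Three further qualifications stand.

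- The 1-to-243 range assumes that the score is the raw level. Section 2.7 does not say so, although no other dimension values are printed.
- A reader might infer that the waitlist arm will have zero QALYs. That follows only from a literal reading of the time term. The next sentence speaks only of years, an earlier one of time spent in a health state, and section 3 (Expected results) refers to the T0–T1 comparison period.
- A reader might infer that a single coefficient, say the one at T1, is applied to the whole interval, which would double a linearly accruing gain. The article states no such rule. It lists collection at T0 and T1, and interpolation between visits is detail that an article commonly leaves to the analysis plan.

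**Conclusion.** The point holds as a wrong stated rule that contradicts the rest of the article. With the printed levels as scores, the coefficient runs from 1 (best) to 243 (worst), reverses direction and lies off the utility scale for all states but one. Whatever the coding, a product of dimension scores is not the value-set index that section 2.6.2 calls for.

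The time term is a wording defect whose effect depends on its reading: zero waitlist QALYs if taken literally, none if elapsed time is meant. The product error remains either way.

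If the formula were followed, the incremental QALYs, the cost-effectiveness ratio, the planes and the acceptability curves at T1 would be invalid. It would go too far to say that the T1 cost-effectiveness objective cannot be answered, since the usable method is already named and EQ-5D-3L is scheduled at T0 and T1 in both arms. The primary outcome, pain acceptance at T1, is untouched. The QALY magnitudes rest on assumed utilities (0.3 to 0.8), assumed gains (0.02 to 0.10) and a 7-week interval.

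**What to change.** In section 2.7, delete the sentence giving the formula and the sentence that multiplies the dimension scores. Replace them with a statement that:

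1. each EQ-5D-3L health state is mapped to its utility index with the country-specific value set, as section 2.6.2 already says, naming the Italian set;
2. QALYs are utility times elapsed time over the same T0–T1 interval in both arms, computed as the area under the line joining the T0 and T1 utilities;
3. the between-arm QALY difference is adjusted for T0 utility.

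The first item and the common elapsed time in the second correct the error. The area calculation and the baseline adjustment could equally be placed in the statistical analysis plan, which should be checked for the same formula.

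The cost is a rewording of two sentences. No new data, visits or participants are needed.
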